Single-component interventions are known to have limited impacts on long-term growth outcomes [19]; these limitations were evident in some of our findings from follow-up and replication studies, despite the generally promising findings from the *Lulun Project*. In the *Lulun Project II* cohort study, approximately 2 years from baseline, we found evidence of growth faltering, no differences between the egg and control groups in LAZ, and significant declines in LAZ from the endline *Lulun Project* in the egg intervention group relative to the control group [20]. In Malawi, the *Mazira Project* replicated the *Lulun Project* and found that the egg intervention had limited effects on linear growth [21]. Increases in intake of proteins and multiple micronutrients were, however, observed in the egg intervention group [22]. The evidence from Malawi, in particular, demonstrates the importance of understanding contextual implications when translating evidence from one setting to another. It is implied that contextual differences between Ecuador and Malawi including dietary staples, regular consumption of other high-quality ASFs in Malawi, lower stunting prevalence in Malawi, differential infection risks, and better health-related social conditions in Ecuador may have explained the contrasting outcomes in both settings [21, 23]. Particularly, the regular consumption of fish in Malawi means that a single-component intervention with ASFs alone would have limited impacts on growth and nutrition outcomes [21]. In Haiti, however, food insecurity limits consumption of ASFs at the population level [24, 25]. Thus, an intervention incorporating ASFs may result in more positive growth outcomes in this setting. An additional contextual layer to the *Grandi Byen* study is that it recognizes urbanization as a risk factor for poor child health outcomes. Urbanization is an accelerating trend globally. Families throughout the world move to cities seeking education, healthcare, and access to markets and food systems for their children, but often face the limitations of poverty [26, 27]. This current study, distinguished from the *Lulun* and *Mazira* projects which tested the egg intervention in rural settings, may offer insight into overcoming unique urban challenges to child development.

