## Methods/Design

### Overview of study design

*Grandi Byen* is a 4-year, 3-arm RCT which aims to test an integrated nutrition (one egg a day), WASH, and responsive parenting intervention on preventing child stunting and enhancing developmental outcomes. Participants will be assigned to one of the following comparison groups: 1) standard well-baby care (control); 2) nutrition intervention (one egg per day for 6 months); and 3) integrated/multicomponent *Grandi Byen* intervention (responsive parenting, nutrition, WASH + one egg per day for 6 months). This study applies an RCT design to maximize the likelihood of establishing intervention causality and to enable us to triangulate findings across multiple measures. All children in the three arms, will be followed at multiple time points from baseline to endline (12 months) on an array of measures.

Protocols for the *Grandi Byen* study have been reviewed and approved by the Bioethics Committee of the Ministry of Public Health and Population (MSPP) in Haiti (#2021-28) and the Institutional Review Board/Human Research Protection Office at Washington University in St. Louis (# 202101035). This project is funded by the Eunice Kennedy Shriver National Institute of Child Health and Development (NICHD) (R01HD098255-02) and was registered on March 5, 2021 at https://clinicaltrials.gov/ (NCT04785352).

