#### Economic evaluation

Economic assessments are specifically tied to the study’s fourth aim. To compare the efficiency of the interventions, we will conduct a cost-effectiveness analysis (CEA) to compare arm 2 to arm 1 and arm 3 to arm 2. The difference in effects (E2-E1 or E3-E2) divided by the corresponding cost difference (C2-C1 or C3-C2) constitutes the incremental cost-effectiveness ratio (ICER) [96, 97]. E1 and C1 are treated as zero for standard well-baby care. C2 and C3 are per participant costs of each respective intervention, while E2 and E3 are mean impacts for relevant study outcomes, such as LAZ or ASQ scores. Thus, multiple ICERs are reported, one for each outcome. If the ICER for 3 vs. 2 is less than the ICER for 2 vs. 1, then the costs of the more intensive intervention are offset by improvements in outcomes and arm 3 is an efficient use of resources.

For broader generalizability, we will also aggregate all study outcomes by conducting a basic cost-benefit analysis (CBA) in which non-overlapping outcome changes for arms 2 and 3 are valued in terms of local currency. Several CBA studies on nutrition in Haiti exist [98, 99] and will provide valuation estimates for most of our study outcomes, as well as a benchmark for the efficiency of this study’s intervention relative to other child health interventions in Haiti. For the CBA, B2 and B3 are the sum of all effects (E2 and E3) for the respective study arms, valued in Haitian gourdes. Benefit-cost ratios reflect efficiency (B2/C2, B3/C3), while net differences indicate how much, if any, an arm improves net welfare [(B2-B1)-(C2-C1)] and [(B3-B2)-(C3-C2)].

For both types of economic evaluation, we will conduct sensitivity analysis of the estimates using both simple 1-way (min/max) and Monte Carlo (multi-way, probabilistic) approaches to reflect statistical confidence intervals in study impacts and costs. In the CEA, costs and effects are measured in a single year, but in the CBA, benefits include a “stream” of gains (estimated into the future) and must be discounted following standard guidelines of 3-12% [96, 97, 99], a factor also included the sensitivity analysis.

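### The sensitivity analyses described for the cost-benefit projection do not vary how long the effect lasts, although the egg trial being replicated showed no LAZ difference at about 2 years

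*Protocol article*

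**What the plan says.** Under Statistical analyses, Economic evaluation, the protocol article plans two evaluations for Aim 4.

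- **Cost-effectiveness analysis.** It has no projection: "In the CEA, costs and effects are measured in a single year".
- **Cost-benefit analysis.** "B2 and B3 are the sum of all effects (E2 and E3) for the respective study arms, valued in Haitian gourdes". Unit values come from existing Haitian studies, which "will provide valuation estimates for most of our study outcomes". It then projects: "in the CBA, benefits include a “stream” of gains (estimated into the future) and must be discounted following standard guidelines of 3-12" per cent.

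One-way (min/max) and Monte Carlo sensitivity analyses are planned for both, "to reflect statistical confidence intervals in study impacts and costs". The discount rate is "a factor also included the sensitivity analysis". The section mentions no horizon, decay or duration of effect.

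Three other places bear on this:

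- **Overview of study design.** Children in all arms "will be followed at multiple time points from baseline to endline (12 months". Eggs are given for 6 months, so the last visit is about 6 months after they stop.
- **Egg and nutrition trials.** In the follow-up of the Ecuador egg trial, "approximately 2 years from baseline, we found evidence of growth faltering, no differences between the egg and control groups in LAZ". LAZ also fell significantly in the egg group relative to control after that trial's endline, and single-component interventions are said to have limited long-term effect on growth.
- **Study aims and hypothesized pathways.** Aim 1 sets out to replicate that trial. For the multicomponent arm, the authors theorise that continued feeding of animal-source foods will sustain the gains.

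**The concern.** A confidence interval for an effect measured by month 12 carries sampling error. It says nothing about loss of effect after month 12. A discount rate weights a future gain by when it occurs, not by whether it occurs. Neither of the named sources of variation therefore reaches the scenario that the article's own background reports for LAZ after eggs alone: a difference at the end of the intervention and none at about 2 years. The last visit falls before that time, so the trial's own data cannot supply the answer.

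Aim 4 asks whether the added benefits are favourable relative to the added costs. The benefit-cost ratios B2/C2 and B3/C3, and the net differences (B2-B1)-(C2-C1) and (B3-B2)-(C3-C2), all contain the projected stream. Their reported range could exclude an outcome the team has already seen once. The contrast between the multicomponent and egg arms is exposed in a particular way, because sustained effect is one of the advantages theorised for the multicomponent arm.

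**Working it through.** The article states no benefit-cost ratio, net benefit, horizon or unit value, so there is no figure of the plan to reproduce. What follows is an illustration on stated assumptions.

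**Inputs.** From the article: discount rate r from 3% to 12%; LAZ effect absent at about 2 years; hypothesised LAZ gains of 0.30 (egg versus standard care) and a further 0.10 (multicomponent versus egg). Assumed: horizons T of 5, 10, 30 and 50 years; one unit of benefit per year, starting at once.

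**Formula.** Present value of a stream lasting T years: A(r,T) = sum over t = 1 to T of 1/(1+r)^t.

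Stopping after year 2:
- at 3%: 1/1.03 + 1/1.03² = 1.91
- at 12%: 1/1.12 + 1/1.12² = 1.69

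| Horizon (years) | Lasting, 3% | Lasting, 12% | Lasting / stops at 2 years, 3% | Same, 12% | Effect of discount rate (3% / 12%) |
|---|---|---|---|---|---|
| 5 | 4.58 | 3.60 | 2.4 | 2.1 | 4.58/3.60 = 1.3 |
| 10 | 8.53 | 5.65 | 4.5 | 3.3 | 8.53/5.65 = 1.5 |
| 30 | 19.60 | 8.06 | 10.2 | 4.8 | 19.60/8.06 = 2.4 |
| 50 | 25.73 | 8.30 | 13.4 | 4.9 | 25.73/8.30 = 3.1 |

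For benefits that start at once, duration moves the value more than the whole 3-12% discount range does, at every horizon tried.

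**Benefits that start late.** If gains accrue only in years 18 to 60, a lasting effect is worth 14.51 at 3% and 1.20 at 12%, a factor of 14.51/1.20 = 12.1. Here the discount rate matters a great deal. If those gains depend on a LAZ difference that has gone, they are zero at either rate.

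**Direction for the arm contrasts (LAZ part only).** Take the hypothesised gains as additive: 0.30 for the egg arm and 0.30 + 0.10 = 0.40 for the multicomponent arm, each against standard care. Use T = 10 and r = 3%, in discounted LAZ-years:

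- Egg arm, lasting: 0.30 × 8.53 = 2.56. Stopping after year 2: 0.30 × 1.91 = 0.57.
- Multicomponent minus egg, both lasting: 0.10 × 8.53 = 0.85.
- Multicomponent lasting, egg stopping: 0.40 × 8.53 - 0.30 × 1.91 = 3.41 - 0.57 = 2.84.
- Both stopping: 0.10 × 1.91 = 0.19.

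At 12% the last three are 0.10 × 5.65 = 0.57; 0.40 × 5.65 - 0.30 × 1.69 = 1.75; and 0.10 × 1.69 = 0.17. If both arms are assumed to last, the egg arm's LAZ benefit is overstated whenever the egg effect fades. The increment of the multicomponent arm over the egg arm may be overstated (both fade) or understated (only the egg arm fades).

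**The case against.** The strongest reply is that this is a short account of a basic cost-benefit analysis in a journal article. The text does not say that its list of sensitivity factors is complete, and it nowhere says that effects are carried forward as constant or permanent. The cited valuation studies, which are not at hand, may already build in attenuation. All of that stands, and a reader who infers that the plan assumes permanent effects, or rules out any other sensitivity factor, goes beyond the text. What remains is that the article does state the purpose and factors of its sensitivity analysis, and they do not reach the fade-out reported in its own background.

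Second, the evidence is narrow. It concerns LAZ, after eggs alone, in a rural Ecuadorian trial. It does not show that developmental gains fade, nor that the multicomponent arm's effect does. The inference that the egg effect as a whole disappears, or that Aim 4 as a whole overstates net benefit, is therefore not supported.

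Third, the text does not say that the projection starts from the 6-month effect. Effects measured up to the 12-month endline would already reflect some early loss.

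Fourth, the consequence is limited. Aims 1 and 2 are the primary aims, and the cost-effectiveness analysis uses no future stream. Both are untouched.

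**Conclusion.** The point holds in a limited form. The described sensitivity analyses omit effect duration, and the article's own background gives a concrete reason to vary it. For the LAZ-based part of B2, net benefit can be overstated. For the multicomponent versus egg contrast the direction is open: if the multicomponent arm sustains its effect, as theorised, and the egg arm does not, the net-welfare difference is understated.

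The size cannot be taken from the document. The ratios of 2.1 to 13.4 in the illustration rest on assumed horizons of 5 to 50 years, a constant benefit starting at once, and complete loss after year 2. They show that duration can matter as much as the factors already listed. They do not estimate the error in this trial. This is a worthwhile improvement to a supporting analysis under Aim 4, not a flaw in the primary analyses.

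**What to change.** In the cost-benefit analysis:

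1. State the benefit horizon, and say whether the borrowed unit values already include attenuation, so that fade-out is not counted twice.
2. State that the stream starts from the 12-month between-arm effect. This is a clarification, since the article does not name the time point.
3. Add persistence of effect to the planned one-way and Monte Carlo analyses, separately by arm and by outcome (LAZ and developmental scores). The range should run from full persistence to a scenario with no LAZ effect by about 24 months from baseline, and should include the case in which only the egg arm fades.
4. Report, for each arm contrast, the persistence at which net benefit is zero, and word the efficiency conclusion accordingly.

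The cost is one more set of parameters in runs already planned, with no new data. The drawback is a wider, and possibly less favourable, range of benefit-cost ratios.

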## Discussion

This paper details the study protocol for the *Grandi Byen* study, a three-arm longitudinal RCT which will test the effectiveness of an integrated nutrition, responsive parenting, and WASH intervention on preventing stunted child growth and promoting neurobehavioral development. Although significant progress has been made in improving early child growth and development worldwide, disparities remain, and stunted child growth still ranks as a leading risk factor in the global burden of disease [100]. In 2012, the World Health Assembly set a target to reduce the absolute number of global child stunting cases to approximately 100 million by 2025 [101]. However, given current trends with the slow decline of child stunting prevalence, projections indicate that the global community might fail to meet this target by 27 million children [2, 101]. The urgency of this issue calls for research on transdisciplinary solutions, integrating expertise across multiple sectors, that target child nutrition as well as other proximal environmental and psychosocial factors that threaten holistic child well-being. The *Grandi Byen* study exemplifies an integrated approach offering insights into complex biological and psychosocial mechanisms, as well as feasible solutions, to confront stunted growth and development.

In conclusion, the *Grandi Byen* project adopts a “novel” conceptualization of holistic child well-being beyond growth outcomes and has the potential to provide insights into complex biological and psychosocial mechanisms that may inform evidence-based solutions against stunted growth and development. The project pools multidisciplinary concepts and frameworks from public health, social work, psychiatry, developmental psychology, infectious diseases, and radiology, merging methods to produce comprehensive perspectives and probe the underlying mechanisms of child development to enhance future interventions. This study combines key innovations implicated in healthy growth and development among children living in poverty.

## Data Availability

Data collected for this project will be made available upon appropriate ethics/human subjects research approval and reasonable request from the study's principal investigators ([name] and [name]), following the publication of the primary results from the trial. We anticipate that primary endpoint analyses will be completed within 24 months of endline data collection for the study’s final cohort.

## Abbreviations

ASF: Animal-source foods
ASQ: Ages and Stages Questionnaire
ASQ-SE: Ages and Stages Questionnaire-Social Emotional
BAZ: Bone age Z-score
CBA: Cost-benefit analysis
CEA: Cost-effectiveness analysis
CRP: C-reactive Protein
DHA: Docosahexaenoic acid
ETEC: Enterotoxigenic *Escherichia coli*
HGLM: Hierarchical generalized linear modeling
HLM: Hierarchical linear modeling
HOME: Home Observation Measurement of the Environment
ICC: Intraclass correlation coefficient
ICER: Incremental cost-effectiveness ratio
IGF-1: Insulin-like growth factor 1
IgE: immunoglobulin E
LAZ: Length-for-age Z-score
MAR: Missing at random
MCAR: Missing completely at random
MSPP: Ministry of Public Health and Population (Ministère de la Santé Publique et de la Population)
NICHD: Eunice Kennedy Shriver National Institute of Child Health and Development
NIH: National Institutes of Health
PICCOLO: Parenting Interactions with Children: Checklist of Observations Linked to Outcomes
RCT: Randomized controlled trial
WASH: Water, sanitation, and hygiene
WAZ: Weight-for-age Z-score
WHZ: Weight-for-height z-score
